#### Procedure for unblinding if needed {17b}

The design is open label with only outcome assessors being blinded, so unblinding will not occur.

### Data collection and management

#### Plans for assessment and collection of outcomes {18a}

On the start day of the study, the research staff will confirm the parent/caregiver’s willingness to allow their child’s continued participation in the study and administer a purpose-designed electronic questionnaire to the parents/caregivers. The questionnaire will cover information such as socio-demographic, health and residence characteristics, history of de-worming and prior malaria treatment. Height/length (cm) and weight (kg) of each child will be measured and anthropometric indices, height-for-age, weight-for-age, weight-for-height and body mass index, will be calculated using the WHO AnthroPlus software (www.who.int/growthref/tools/en/). The study villages will be mapped by recording each study participant’s household global positioning system (GPS) coordinates with a hand-held GPS device.

The quantitative study will be implemented in collaboration with the SMC and NTD providers during the SMC campaign which will start in Saraya district by the middle of June 2022. Two hundred children pre-school and school-age children will be enrolled into each arm of the study as described above. The study procedures are illustrated in Fig. 2 and Table 2. The children will be evaluated one  month after the last course of SMC cycles at the end of malaria transmission season to measure haemoglobin concentration and to obtain a further blood film, dried blood spot, stool and urine samples.

**Table 2 Tab2:** Schematic diagram of the study procedures

SMC cycle	1					2, 3 and 4	End of malaria season
Timelines (days)	Day 0–1	Day 0	Day 1	Days 2 and 3	Days 4–6		
**Study procedures**						**Passive surveillance**	
Informed consent ± assent	X						
Enrolment and questionnaire administration to parent/caregivers		X					
Distribution of collecting bottles for stool sample	X						
Sample collection (finger-prick blood, urine, stool)		X					
**Randomisation**		X					
Group 1: vitamin A + zinc		X	AQ + SP	AQ			
Group 2: PZQ + vitamin A		X	AQ + SP	AQ			
Group 3: ALB + PZQ		X	AQ + SP	AQ			
Safety assessments		X	X	X	X		
**Post-intervention survey**							X
Sample collection: finger-prick							X
Sample collection: stool							X
Sample collection: urine							X

Qualitative interview participants will be 50 randomly selected parents/caregivers of study children, 10 SMC/MDA implementation staff and six SMC/NTD programme managers. The participants will be segregated by gender to allow free expression of views within each homogenous group. A purpose-designed guide will be used to facilitate these sessions. The proceedings of the sessions will be audio-recorded following verbal consent by the participants. These will be transcribed into texts by trained research assistants.

#### Plans to promote participant retention and complete follow-up {18b}

A reminder system will be implemented using short text messages (SMS) delivered via mobile telephones to all health centres staff reminding them to regularly look out for the study participants, asking them to report any serious events. A phone credit will be provided to the staff as an incentive, and they will be contacted after each SMC round to confirm whether they have observed any adverse events. The health post staff will be linked to a member of the study team who will contact them by phone or in person throughout the study to maintain contact, ask about any problems, give support and advice and remind them about study procedures using a standardised list of reminders.

#### Data management {19}

All data will be collected using encrypted android tablets and subsequently transferred to the University of Thies’ encrypted RedCap server in Senegal. Following export, they will be held on LSHTM’s network drive (in a personal area restricted to the project team) and accessed using encrypted laptops. All data generated in this project will be managed in accordance with the LSHTM Information Management and Security Policy, which has been drawn up in line with ISO/IEC 27001 and other relevant legal, procedural and technological requirements.

#### Confidentiality {27}

All study children will be assigned a unique number, which will be used as an identifier throughout the study. Participant data will be securely stored in the dedicated study’s computer devices, which will be accessible only with a password. All laboratory results and adverse event data will be encoded in an electronic database and stored securely by the PI or designee. Only authorised study personnel will have access to the study data.

The collection and processing of personal data from the participants enrolled in this study will be limited to those data that are necessary to fulfil the objectives of the study. These data will be collected and processed with adequate precautions to ensure confidentiality and compliance with applicable data privacy protection laws and regulations. Appropriate technical and organisational measures to protect the personal data against unauthorised disclosures or access, accidental or unlawful destruction, or accidental loss or alteration will be put in place.

#### Plans for collection, laboratory evaluation and storage of biological specimens for genetic or molecular analysis in this trial/future use {33}

Prior to the administration of study drugs, finger-prick blood samples will be collected from the participants for preparation of thick and thin blood smears for malaria microscopy, and blood spots will be collected on Whatman filter papers for DNA isolation and PCR amplification for species determination. Freshly voided urine samples will also be collected from all study children. The urine filtration test will be used to quantify *S. haemotobium*, according to WHO guidelines. Parallel testing for circulating cathodic antigens (CCA) will be used to complement the filtration test [25]. The urine CCA dipstick test has been extensively used in SSA and has sensitivity and specificity values for *S. mansoni* ranging from 52.5 to 63.2% and 57.7 to 75.6%, respectively [26, 27].

Faecal samples will be collected to detect intestinal helminths. Duplicate Kato-Katz thick smears will be produced from the stool samples and examined by experienced technicians using light microscopy to determine the egg counts for *S. mansoni* and STH. The numbers of eggs per slide will be used to obtain a measure of the number of helminth eggs per gramme of faeces (EPG). The intensity of the helminth infection will be categorised according to WHO guidelines [28]. A multiplex PCR assay will also be used for simultaneous detection of mixed infections of helminths [29]. Quality control will be performed by re-examining at least 10% randomly selected blood slides, urine filters and Kato-Katz smears by an experienced independent lab scientist. Haemoglobin concentrations will be measured using the Haemocue® haemoglobin analyzer. Duplicate dried blood spots will be shipped to LSHTM for Luminex multiplex immunoassays [30].

### Statistical methods

#### Statistical methods for primary and secondary outcomes {20a}

Infection intensities of positive samples will be calculated as the geometric mean of parasites per microlitre of blood for and geometric mean of eggs per gram of faeces for *S. mansoni*. For *S. haematobium*, infection intensity will be calculated as geometric mean of eggs per 10ml of urine. For pre- and post-intervention time points, the chi-square test will be used to compare proportions (prevalence) of malaria infection and prevalence of anaemia between the intervention and control groups. Similarly, for each time point, the Student *t*-test will be used to compare geometric mean parasite counts and mean haemoglobin concentrations between the intervention and control groups. The repeated measures analysis of variance will be used to compare geometric mean parasite counts and mean haemoglobin concentrations where repeated measurements for pre- and post-intervention time points are compared. All statistical tests will be two-sided at a significance of alpha < 0.05.

Qualitative data will be managed by NVivo software version 12.0 and analysis will be done by initially coding the main themes that emerge from the transcribed texts. The themes will subsequently be sorted and collated into categories and sub-categories. Hypotheses and concepts will be developed inductively from the themes. The findings of the qualitative and quantitative data addressing similar concepts will be triangulated in the final report.

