**Methods:**

This study will have quantitative and qualitative components. The quantitative component will be a three-arm, observer-blind, placebo-controlled, interventional study of co-administration of SMC and anthelminthic drugs to pre-school and school-age children in Saraya district, southeast Senegal. Six hundred children aged 1–14 years will be randomly assigned to receive either SMC drugs only, SMC drugs and praziquantel or SMC drugs and albendazole and praziquantel at a ratio of 1:1:1. The primary outcome will be solicited and unsolicited adverse reactions to the study medications. The secondary outcomes will be the prevalence and intensity of *Plasmodium*-helminth co-infection and the prevalence of anaemia and mean haemoglobin concentration.

The qualitative component of the study will include the conduct of structured interviews to assess the acceptability, feasibility, enablers and barriers to the combined use of anthelminthic and SMC drugs among randomly selected parents/caregivers of children enrolled in the study and health care workers responsible for the delivery of the combined services.

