#### Secondary outcomes

Prevalence and intensity of *Plasmodium*-helminth co-infectionFaecal egg counts for each of the four parasites (hookworm, *A. lumbricoides*, *T. trichiura*, *and S. mansoni*) and urine egg count for *S. haematobium* will be recorded, and the prevalence and arithmetic mean intensity of *Plasmodium* infection will be calculated before and after concurrent administration of SMC and anthelminthic drugs (i.e. at the end of malaria transmission season).Prevalence of anaemia and mean haemoglobin concentrationHaemoglobin concentration of all children will be checked using a HemoCue® haemoglobin analyser, before and after co-administration of SMC and anthelminthic drugs (i.e. at the end of malaria transmission season).

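### Infection intensity is defined in positive samples only and then compared between arms after treatment, which selects on a post-randomisation outcome; for Plasmodium the summary measure also conflicts with the outcome definition.

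*Protocol article*

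**What the plan says.** The abstract lists intensity among the secondary outcomes: "The secondary outcomes will be the prevalence and intensity of" Plasmodium-helminth co-infection. Section {20a} of the protocol article fixes how intensity is summarised: "Infection intensities of positive samples will be calculated as the geometric mean of parasites per microlitre of blood", and likewise for S. mansoni eggs per gram. For S. haematobium, "infection intensity will be calculated as geometric mean of eggs per 10ml of urine"; the restriction to positives is not repeated there, and no rule is given for zero counts.

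Two tests follow. At each time point, before and after the intervention, a Student t-test will "compare geometric mean parasite counts and mean haemoglobin concentrations between the intervention and control groups". For change over time, "The repeated measures analysis of variance will be used to compare geometric mean parasite counts and mean haemoglobin concentrations".

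The Secondary outcomes section uses a different summary for malaria, "the prevalence and arithmetic mean intensity of" Plasmodium infection. It says that helminth egg counts will be recorded but names no mean for them.

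The chi-square test in {20a} is there to "compare proportions (prevalence) of malaria infection and prevalence of anaemia between the intervention and control groups"; helminth prevalence is not named. Section {20c} promises an intention-to-treat analysis of everyone randomised.

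**The concern.** Praziquantel goes to two arms and not to the control arm (Fig. 2 legend, Table 2). A child's positivity at the end of the season is therefore partly a result of allocation. Restricting the intensity comparison to positives sets treated children whose infection persisted or returned against all infected controls, and these groups are not exchangeable. A cleared child has a valid result, a count of zero, but contributes nothing.

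Clearing infection is a main way in which an anthelminthic could act, so the intensity comparison could miss such an effect. If the positives-only definition carries into the repeated measures analysis, children cleared between surveys would drop out there as well. Separately, arithmetic and geometric means of skewed counts can differ greatly, so the Plasmodium intensity outcome as written has two different definitions.

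**Working it through.** **Inputs from the article.** Sample size {14}: infection prevalence 30% versus 16%, 90% power, 188 per arm, 200 enrolled per arm, 10% loss. Trial design {8}: pre-season prevalence by community 3.3–9.5% for malaria and 12.2–64.8% for schistosomes. Section {20a}: two-sided 5% tests.

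**The plan's own figure.** Pooled two-proportion formula, mean proportion 0.23: n = [1.960 × √(2 × 0.23 × 0.77) + 1.282 × √(0.30 × 0.70 + 0.16 × 0.84)]² / 0.14² = 187.8, so 188 per arm, as stated. The relative risk is 0.16/0.30 = 0.53, a 47% reduction. No sample size is given for intensity.

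**Children left in a positives-only comparison**, with 200 × 0.9 = 180 evaluable per arm:
- Any infection: 180 × 0.30 = 54 versus 180 × 0.16 ≈ 29.
- Malaria at the surveyed prevalence: 180 × 0.033 ≈ 6 to 180 × 0.095 ≈ 17.
- Schistosomes in the control arm: 180 × 0.122 ≈ 22 to 180 × 0.648 ≈ 117.

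**Clearance unrelated to intensity.** The remaining positives are a random subset of the infected, so their log counts have the same distribution as in controls and the geometric mean ratio is exp(0) = 1.0. The arithmetic mean over all children has ratio 0.53.

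**Only the lightest 47% of infections clear** (log-normal counts, no egg reduction in the rest). The mean of a standard normal above z = −0.075 is φ(z)/0.53 = 0.3978/0.53 = 0.7506, so the ratio in positives is exp(s × 0.7506). Assumed log-SDs s of 1.0, 1.5 and 2.0 give 2.1, 3.1 and 4.5. This is an upper bound at 47% clearance.

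**Simulation**, 180 per arm, 1,500 runs per scenario. Assumed, not in the documents: log mean 3.0, log-SD 1.5 and the clearance patterns shown. The positives-only analysis is a t-test on log counts; the all-children analysis is a t-test on log(count + 1). Each cell gives results at control prevalence 12.2% / 30% / 64.8%.

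| Pattern in treated arm | Ratio, positives | Test in positives | Ratio, all children | Power, all children |
|---|---|---|---|---|
| 47% cleared at random | 0.97 / 1.00 / 0.99 | rejects 5 / 4 / 6% | 0.47 / 0.41 / 0.29 | 42 / 83 / 100% |
| 70% cleared at random | 0.99 / 1.01 / 1.00 | rejects 4 / 6 / 5% | 0.25 / 0.21 / 0.13 | 82 / 100 / 100% |
| 90% of light, 50% of heavy cleared | 2.2 / 2.2 / 2.2 | significant in wrong direction 19 / 49 / 82% | 0.33 / 0.27 / 0.17 | 67 / 97 / 100% |
| Same, plus 30% egg reduction in the rest | 1.5 / 1.5 / 1.6 | significant in wrong direction 7 / 16 / 37% | 0.29 / 0.24 / 0.15 | 74 / 99 / 100% |
| 70% cleared at random, plus 60% egg reduction in the rest | 0.43 / 0.44 / 0.43 | right direction, power 21 / 49 / 84% | 0.19 / 0.15 / 0.09 | 92 / 100 / 100% |

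**The case against.** The best defence is that intensity in positives complements prevalence. Prevalence is also a secondary outcome, one of the two sample-size calculations rests on infection prevalence, and section {33} classes helminth intensity by WHO category. A reader might infer that the plan ignores cures altogether. The documents do not support that, because clearance would show in a prevalence comparison. What stands is that {20a} names its proportion test for malaria and anaemia only.

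Other parts of the objection also hold:
- The conflict between arithmetic and geometric means is explicit for Plasmodium only. The documents show no such conflict for helminths.
- Parasite counts in the t-test sentence may mean malaria only. The same selection would then apply to Plasmodium, and no between-arm test of helminth intensity would be stated.
- That the repeated measures analysis keeps only children positive at both surveys is an inference from the definition, not something the article says.
- The plan's 47% refers to any malaria or helminth infection and serves here only as an illustration. Infections acquired between the June dosing and the end-of-season survey are not modelled.
- Small numbers are a problem for malaria. They are not a general one for schistosomes, with about 22–117 control positives.

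Finally, intensity is secondary in a safety trial, and the Discussion says that measuring efficacy probably needs a larger study. That limits the weight of the point but does not remove it. The measure, the positives-only set and the test are stated here, so this is not detail left to an unseen analysis plan.

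**Conclusion.** The point holds in a limited form. A post-intervention comparison of geometric means in positives is not protected by randomisation and does not match the intention-to-treat statement in {20c}. The article gives no zero-inclusive rule, offset or two-part model to compensate. The restriction is stated for blood parasites and S. mansoni. For S. haematobium it is implied, since a geometric mean that includes zeros is zero or undefined without an offset.

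If treatment mainly clears infections regardless of intensity, the positives-only ratio is about 1.0 and the test rejects at about its nominal error rate. A reader might infer that the plan will show deworming as harmful. That needs light infections to clear preferentially, and the figures of 2.1, 3.1 and 4.5 further require perfect truncation, the assumed log-SDs and no egg reduction in uncleared infections. Where uncleared infections also shed far fewer eggs, the direction is right and the cost is power.

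For Plasmodium, the arithmetic and geometric definitions contradict each other and must be reconciled. As a secondary-outcome matter, this should be corrected.

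**What to change.** - Name one summary measure for intensity in both the Secondary outcomes section and {20a}.
- Compare post-intervention counts in all randomised children with a result, zeros included. Negative binomial regression or an analysis of log(x + 1), adjusted for baseline count and age group, would serve; a two-part model would also meet the objection.
- State that the comparison covers helminth egg counts as well as malaria parasites.
- Add helminth prevalence to the between-arm proportion test.
- Report positives-only geometric means descriptively, without a between-arm test.

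The planned blood, stool and urine samples already supply the counts, so no new data are needed. The cost is wording and slightly more analysis work. The change will not make malaria intensity precise: about 6–17 positives of 180 per arm at the surveyed pre-season prevalence remain few under any model.

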**Fig. 1 Fig1:**
[figure not shown]
Map of Senegal showing the study site. Source: https://www.cia.gov/resources/map/senegal/. Terms of use: https://www.cia.gov/site-policies

In June 2021, prior to the start of the malaria transmission season and before SMC administration commenced, we conducted a population-based survey to estimate the prevalence of malaria-helminth co-infections among children aged 1–14 years in 18 villages in Saraya district. Preliminary findings of this survey showed that the prevalence of malaria ranged between communities from 3.3 to 9.5% and of *Schistosome* infection from 12.2 to 64.8% (unpublished data). These findings will guide the selection of the villages for implementing the study described in this protocol. The schematic diagram of the study design is illustrated in Fig. 2.

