### Assignment of interventions: allocation

#### Sequence generation {16a}

Randomisation will be used to minimise bias in the assignment of eligible children to the study arms to increase the likelihood that known and unknown attributes (e.g. demographic and baseline characteristics) are evenly balanced across arms and to enhance the validity of possible statistical comparisons across arms. Randomisation will be performed by a study pharmacist in blocks of 3 using a table of random numbers and will be stratified by age groups.

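### Post-season haemoglobin and prevalence are compared without baseline value or age stratum, and the added repeated-measures ANOVA is less precise than ANCOVA and leaves its treatment term unnamed

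*Protocol article*

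**What the plan says.** Three pieces of analysis are fixed in the protocol article, section {20a}.

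- Prevalence: "For pre- and post-intervention time points, the chi-square test will be used to compare proportions", and the outcomes named for it are malaria infection and anaemia.
- Haemoglobin and parasite counts: separately before and after treatment, a Student t-test that "will be used to compare geometric mean parasite counts and mean haemoglobin concentrations between the intervention and control groups".
- Pre and post together: "The repeated measures analysis of variance will be used to compare geometric mean parasite counts and mean haemoglobin concentrations where repeated measurements" at the two time points are compared. The model term that measures the treatment effect is not named.

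All tests are two-sided at 5%. Section {20b} foresees no further analyses.

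Elsewhere, the Outcomes section {12} has haemoglobin measured in all children before treatment and again at the end of the transmission season, and Table 2 has blood, urine and stool collected on day 0. The Sequence generation section {16a} randomises in blocks of 3 and says that allocation "will be stratified by age groups". Neither the baseline value nor the age stratum enters any of the planned tests as an adjustment.

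**The concern.** The children are aged 1 to 14 years. Haemoglobin before treatment is likely to predict haemoglobin a season later, and age may predict it as well. A comparison that ignores both leaves explainable variation in the error term. When randomisation is balanced on age by small blocks, an analysis that omits age also overstates the standard error.

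The repeated-measures ANOVA does not repair this. With two time points, its group-by-time term is the same as a t-test on change scores, which is never more precise than ANCOVA. Its group main effect averages the follow-up difference with a baseline at which no treatment has been given. The post-season t-test and the ANOVA also stand side by side for haemoglobin without a stated order, and section {17a} leaves the data analyst unmasked.

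Significance tests between arms before treatment say nothing about the treatment effect. Sections {16b} and {16c} plan no allocation concealment and have the enrolling assistants assign the arms, so a real imbalance cannot be excluded. Adjusting for baseline would deal with that better than testing it and then comparing the arms unadjusted.

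**Working it through.** **Inputs from the Sample size section {14}:** haemoglobin 10.5 g/dl against 11.0 g/dl (difference 0.5), SD 1.5, power 90%, two-sided 5%; prevalence 30% against 16%; 200 enrolled per arm with 10% loss, so 200 × 0.9 = 180 evaluable. **Assumed:** a pre/post haemoglobin correlation r, which the protocol does not give, shown at 0.3, 0.5 and 0.7.

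**Reproducing the plan's figures.**
- Haemoglobin: n = 2 × 1.5² × (1.960 + 1.282)² / 0.5² = 189.1 per arm (stated: 189).
- Prevalence: n = [1.960√(2 × 0.23 × 0.77) + 1.282√(0.30 × 0.70 + 0.16 × 0.84)]² / 0.14² = 188 per arm (stated: 188).

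Both sizes rest on an unadjusted comparison after treatment.

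**Power at 180 per arm (noncentral t).** The standard error is SD_eff × √(2/180). For the post-season t-test, SD_eff = 1.5, the standard error is 0.158, and 0.5 / 0.158 = 3.16, which gives 88.4%.

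| Analysis | SD_eff | Effect estimated | r = 0.3 | r = 0.5 | r = 0.7 |
|---|---|---|---|---|---|
| Post-season t-test | 1.5 | 0.5 | 88.4% | 88.4% | 88.4% |
| ANCOVA on baseline | 1.5√(1 − r²) | 0.5 | 91.1% | 95.4% | 99.3% |
| ANOVA, group by time | 1.5√(2(1 − r)) | 0.5 | 76.0% | 88.4% | 98.3% |
| ANOVA, group main effect | 1.5√((1 + r)/2) | 0.25 | 49.8% | 44.5% | 40.2% |

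The group main effect estimates (0 + 0.5)/2 = 0.25 g/dl. Simulation (4,000 runs per r) gave mean group effects of 0.247 to 0.252 and power close to the table.

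**Why ANCOVA is never worse than group by time.** 1 − r² = (1 − r)(1 + r), and 1 + r ≤ 2, so 1 − r² ≤ 2(1 − r). Group by time also falls below the plain t-test when 2(1 − r) > 1, that is, when r < 0.5.

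**Children per arm for 90% power** (r = 0.3 / 0.5 / 0.7): ANCOVA 173 / 142 / 97; group by time 265 / 190 / 114; unadjusted t-test 190.

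**Age strata.** If balanced strata explain a share R² of haemoglobin variance, the unadjusted test's true type I error is 2[1 − Φ(1.960/√(1 − R²))]. For assumed R² of 0.10 and 0.30 this is 0.039 and 0.019 in place of 0.05. By normal approximation, power is 89.7% and 92.5% unadjusted against 91.5% and 96.6% adjusted. These gains overlap with those from baseline haemoglobin and should not be added to them.

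**The case against.** The strongest reply is that nothing here is invalid. The unadjusted post-season tests are unbiased under randomisation, and ignoring the age strata errs on the conservative side. At r = 0.3 the loss against ANCOVA is under 3 points of power. The larger gains need a correlation of 0.5 to 0.7 across a whole transmission season with treatment in between, and the protocol gives no such figure. At r = 0.2, ANCOVA reaches only 89.6%. The outcomes are secondary, and the Discussion already says that efficacy probably needs a larger study. All of this stands and limits the weight of the point.

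It may also be said that such detail belongs in a statistical analysis plan that is not shown. That holds for the choice of ANOVA term. It does not hold for the tests themselves, which section {20a} names.

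A reader might infer more than the document supports:

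- **That the plan halves the haemoglobin effect.** This happens only if the group main effect is read. The ANOVA is described for comparing pre- with post-intervention measurements, which points rather to time or group by time, and group by time keeps the full 0.5 g/dl.
- **That prevalence is analysed by repeated-measures ANOVA.** It is planned only for haemoglobin and parasite counts.
- **That three analyses compete for post-season haemoglobin.** There are two, because the baseline t-test cannot estimate a treatment effect.
- **That village must be adjusted for.** The wide range, 12.2 to 64.8%, is for schistosome infection, and section {20a} names no chi-square test for that outcome. An even spread over that range would explain (0.526²/12) / (0.385 × 0.615), about 10% of variance. For malaria, section {8} reports that "the prevalence of malaria ranged between communities from 3.3 to 9.5"%, and the same calculation gives (0.062²/12) / (0.064 × 0.936), about 0.5%. Both ranges come from a survey used to choose the trial villages, not from those villages, and village is not a randomisation stratum.

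**Conclusion.** The point holds as one of efficiency and clarity. The post-season t-tests and chi-square tests are sound but leave out information that is already collected. On the protocol's own inputs at 180 per arm, adjusting for baseline haemoglobin raises power from 88.4% to between 91% and 99%. Across the assumed range of r this restores the 90% target without enrolling another child. The size rests on r between 0.3 and 0.7, an assumption, and the gain shrinks towards nothing as r approaches zero. The repeated-measures ANOVA adds nothing that ANCOVA does not do better, and its unnamed treatment term leaves room for misreading.

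The evidence does not show bias or an invalid test. No gain is quantified for malaria or anaemia prevalence, where the argument rests on using the randomisation strata. This is a free improvement on secondary outcomes.

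**What to change.** Name one analysis per outcome in section {20a}.

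- **Haemoglobin:** ANCOVA of the post-season value on arm, baseline haemoglobin and age stratum, reporting the adjusted mean difference with 95% confidence interval for each active arm against SMC alone.
- **Malaria and anaemia prevalence, post-season:** Mantel-Haenszel over age strata, or regression with baseline status and age stratum where there are enough events. At the survey's 3.3 to 9.5% malaria prevalence, 180 children would give about 6 to 17 positives per arm (illustrative, since the survey was pre-season). Mantel-Haenszel is then the safer choice for malaria.
- **Remove** the between-arm significance tests at baseline and the repeated-measures ANOVA. Describe baseline by arm without p-values.
- **Village:** adjustment is optional.

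The cost is wording only. The covariates are already collected, and section {20c} already keeps children with only a pre- or only a post-intervention measurement out of the full analysis set, so baseline adjustment should remove no one further from it.
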